### 2.4. Outcome Assessment

The subjects of both groups will be assessed clinically (intention to treat) by a physical therapist not involved in other phases of the study at baseline (T0), at the end of the treatment (T1), and at 6 months after the acute event (T2). See Figure 1.

### 2.5. Clinical Outcome Measure

#### 2.5.1. Primary Outcome

The FM-UL motor evaluation (0–66) will be considered the primary outcome of the study. The Fugl–Meyer Assessment is a stroke-specific, performance-based impairment index. It is designed to assess motor functioning, balance, sensation, and joint functioning in patients with post-stroke hemiplegia. It is applied clinically and in research to determine the disease severity, to describe motor recovery, and to plan and assess the treatment. In this study, we will consider the motor performance items of the upper extremity (0–66) only, i.e., the FM-UL.

#### 2.5.2. Secondary Outcomes

The secondary outcomes will be based on the ICF:Body function: MAS (shoulder, elbow, and wrist);Activity (capacity/performance): Box and Block Test; Nine Hole Peg Test; Frenchay Arm Test; Modified Barthel Index;Participation: Modified Rankin Scale.

A patient satisfaction questionnaire will be evaluated only in EG at T1.

A change in the spasticity (shoulder, elbow, and wrist) will be measured by the MAS, which measures resistance during passive soft-tissue stretching. Scoring: 0, no increase in muscle tone; 1, a slight increase in muscle tone, manifested by a catch and release or by minimal resistance at the end of the range of motion when the affected part(s) are moved in flexion or extension; 1+, a slight increase in muscle tone, manifested by a catch, followed by minimal resistance throughout the remainder (less than half) of the ROM; 2, a more marked increase in muscle tone through most of the ROM, but affected part(s) easily moved; 3, Considerable increase in muscle tone, passive movement difficult; and 4, affected part(s) rigid during flexion or extension.

Unilateral gross manual dexterity will be measured by the Box and Block Test (BBT). It is a quick, simple, and inexpensive test. The BBT is composed of a wooden box divided into two compartments by a partition and 150 blocks. The BBT administration consists of asking the client to move, one by one, the maximum number of blocks from one compartment of a box to another of equal size within 60 s. The box should be oriented lengthwise and placed at the client’s midline, with the compartment holding the blocks oriented towards the hand being tested. In order to practice and to register baseline scores, the test should begin with the unaffected upper limb. Additionally, a 15 s trial period is permitted at the beginning of each side. Before the trial but after standardized instructions are given to the patients, they should be advised that their fingertips must cross the partition when transferring the blocks and that they do not need to pick up any blocks that might fall outside of the box.

Finger dexterity will be measured by the Nine Hole Peg Test (9HPT) that is administered by asking the client to take pegs from a container, one by one, and to place them into holes on a board as quickly as possible; scores are based on the time taken to complete the test activity, recorded in seconds. Alternative scoring—the number of pegs placed within 50 or 100 s can be recorded. In this case, the results will be expressed as the number of pegs placed per second; a stopwatch should be started from the moment the participant touches the first peg until the moment the last peg hits the container.

Upper extremity proximal motor control and dexterity during ADL will be measured by the Frenchay Arm Test (FAT). The FAT is an upper-extremity-specific measure of activity limitation (activity domain of the ICF). Each item is scored as either pass (=1) or fail (=0). The total scores range from 0 to 5.

Performance in ADL will be measured by the modified Barthel Index (mBI), which is an ordinal scale used to measure ten variables describing ADL and mobility, with a higher number being a reflection of greater ability to function independently following hospital discharge. The 10 items of mobility and self-care ADL are feeding, personal hygiene, bathing, dressing, chair–bed transfer, toileting, bladder continence, bowel continence, ambulation or wheelchair use, and stair climbing. Scoring: the item scores are summed across them in order to compute the total score; a score of 0 indicates total assistance, while a total score of 100 indicates total independence.

The degree of disability or dependence during daily activities will be measured by the modified Rankin Scale (mRS), which is a commonly used scale for measuring disability or dependence in people who have suffered a stroke or other causes of neurological disability. It has become the most widely used clinical outcome measure for stroke clinical trials. The scale runs from 0 to 6, ranging from perfect health without symptoms to death: 0, no symptoms; 1, no significant disability—able to carry out all usual activities, despite some symptoms; 2, slight disability—able to look after own affairs without assistance, but unable to carry out all previous activities; 3, moderate disability—requires some help, but able to walk unassisted; 4, moderately severe disability—unable to attend to own bodily needs without assistance, and unable to walk unassisted; 5, severe disability—requires constant nursing care and attention, and is bedridden and incontinent; and 6—death.

Moreover, an instrumental robotic assessment through the exoskeleton will be carried out only on subjects in the EG:A_FORCE: measures of the force exerted by the patient for each movement;A_MOVE: measures the patient’s 3D work area (paint the walls of the room);A-GOAL: movement functionality.

### 2.6. Neurophysiological Signals

In a subgroup of subjects in the EG, changes in muscle activity will be assessed by surface ElectroMyoGraphy (sEMG) at T0 and T1 during the execution of a standardized motor task (reaching). Specifically, the muscle activity of the following muscles of both the healthy and paretic upper extremity will be acquired: pectoralis major, ascending trapezius, transverse trapezius, medial deltoid, biceps brachii, triceps brachii, flexor carpi ulnaris, and extensor carpi ulnaris. The electrodes should be placed halfway between the origin and insertion, parallel to the muscle fibers, according to SENIAM recommendations [18]. To analyze the amplitude of the surface EMG signal, we will calculate the root mean square, i.e., the square root of the average power of a signal over a given period of time. For this purpose, the raw EMG data will be full-wave rectified and processed using an algorithm with a sliding window of 20 ms. The EMG with the largest rectified and smoothed amplitude will be quantified for a 2 s period during each test. Data from this period will be used to analyze each muscle test performed for normalization.

Moreover, the electroencephalography (EEG) will be assessed as follows: brain electrical activity will be recorded (0.3–100 Hz bandpass, sampling frequency: 512 Hz) from 120 electrodes placed according to the International 10–20 System during resting conditions with the patients’ eyes open and closed (5 min each). A horizontal and vertical electroculogram (0.3–70 Hz bandpass) will be recorded to monitor eye movements. The EEG evaluation will be performed before and after rehabilitation. To eliminate interference from eye, muscle, and cardiac artifacts and other types of noise, the EEG will be fragmented into 2 s epochs, and two procedures will be used: data will be reviewed to manually eliminate epochs with aberrant waves; artifact detection will be completed using an independent component analysis (ICA) algorithm developed in EEGLAB. Private epochs of artifacts will be considered for subsequent analyzes. The frequency bands of interest are delta (2–4 Hz), theta (4–8 Hz), alpha1 (8–10.5 Hz), alpha2 (10.5–13 Hz), beta1 (13–20 Hz), beta2 (20–30 Hz), and gamma (30–40 Hz). For the EEG source analysis, the EEG data will be normalized, and the activation current density of the cortical sources on 6239 voxels will be calculated using standardized low-resolution electromagnetic tomography (sLORETA), available as a free software package. This method is based on the resolution of the inverse problem by reconstructing the cortical distribution of the sources of neuronal electrical activity in three dimensions, starting from the EEG data. Given the low spatial resolution of the method, 12 brain regions of interest (central, frontal, occipital, temporal, and limbic in the right and left hemispheres) will be reconstructed based on the Talairach atlas. An EEG spectral coherence analysis that evaluates functional coupling between the brain areas studied will be implemented using software developed in our laboratory (Matlab, Mathworks Inc., Natick, MA, USA). Brain connectivity will be calculated using eLORETA software for 84 regions of interest defined according to the 42 Brodmann areas for the right and left hemispheres. Using the 84 eLORETA regions of interest, delayed linear coherence will be calculated using the “all voxels closest” method among all possible pairs of regions of interest. The connectivity values will be calculated for each frequency band and for each subject and will be used as the weight of the graph calculated with graph theory. To study connectivity and to track its modulation (graph theory) after rehabilitation treatment, innovative brain network analysis measures will be used. The following parameters will be calculated for the sources of cerebral activation, for each participant, and in each frequency band: The characteristic path length (L) represents a measure of brain integration and is given by the average of the shortest path between each pair of connected nodes. The clustering coefficient (C) represents a measure of brain segregation, quantified as the tendency of the network to form clusters. Small-worldness (S) is the ratio between the normalized C and L.

## 3. Procedure

### 3.1. Control Group

The control group (CG), in addition to multidisciplinary rehabilitation, will follow 40 min of conventional upper limb rehabilitation. Each participant will perform a total of 25 ± 3 conventional upper limb treatment sessions with a frequency of 5 times a week for 5 weeks. Each session will consist of passive, active-assisted, and active exercises tailored for shoulder, arm, and hand motor rehabilitation. For a detailed description of the exercises scheduled, please see Table 1, which shows the Tidier Template for Intervention Description and Replication [19].

### 3.2. Experimental Group

The experimental group (EG), in addition to multidisciplinary rehabilitation, will perform one session per day of exoskeleton-assisted UL-RAT through the Armeo^®^Power (Hocoma AG, CH) robotic system. Each participant will perform a total of 25 ± 3 treatment sessions with a frequency of 5 times a week for 5 consecutive weeks.

During the first session, the device will be adjusted to the patient’s arm size and the angle of suspension. The working space and the exercises will be selected once the upper limb has been fitted with the system. The selection of personalized exercises will be based on the motor skills of each patient, and the difficulty can be gradually increased during training. In particular, a course of exercises has been defined, in which the difficulty varies (the suspension rate; the level of assistance; and the complexity of movement (1D, 2D, and 3D)). The physiotherapist will choose the modality based on the patient’s motor skills (standardized and personalized training); see Table 1.

UL–RAT will be set for 25% of the total weekly regular rehabilitation, in addition to the remaining 75% of tailored multidisciplinary rehabilitation programs, including occupational therapy, speech therapy, and cognitive-neuropsychological therapy. As compared with EG, CG will receive the same amount of neuro-motor rehabilitation each day following traditional rehabilitation approaches.

### 3.3. Safety and Adverse Event Reporting

All safety issues concerning the use of robotics will be applied for this trial. Moreover, the main investigators will report and evaluate suspected adverse events during the training and at follow-up visit.

### 3.4. Data Management

A long-term data sharing and preservation plan will be used to store and make the data publicly accessible beyond the life of the project. The data will be deposited into an online data repository. Before any testing under this protocol, the subjects will also provide all authorizations required by local law (D.Lgs. 196/2003). Each subject will be identified by a code in an unequivocal manner, which will be the identifier of the subject for the duration of the study.

### 3.5. Data Analysis

The sample size was determined based on the data published by Calabrò et al. in 2017 [20]: using a statistical power of 80% and an alpha of 5% with a β error of 20%, we need 70 total subjects (35 EG and 35 CG). However, considering the potential drop-out rate, 20% more, i.e., a total of 84 patients (42 EG and 42 CG), should be enrolled. In the absence of standard values of reference in the literature for the evaluation of the neurophysiological effects of robotic treatment for an upper limb compared with conventional treatment, an interim analysis will be performed when we enroll at least 10 patients of the expected sample. Following the results of the analysis of the acquired neurophysiological signals, we will evaluate whether to continue the enrolment or re-evaluate the number of subjects to be recruited.

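### The drop-out allowance adds 20% to 70, so 84 enrolled keep 70 evaluable only up to 16.7% drop-out; at 20%, about 67 remain (minor)

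*Protocol article*

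**What the plan says.** The sample size paragraph is in section 3.5 (Data Analysis) of the protocol article. It takes its starting point from a study published in 2017 ("The sample size was determined based on the data published by" the authors of that study) and sets the error rates: "using a statistical power of 80% and an alpha of 5% with a β error of 20" per cent. From these it concludes: "we need 70 total subjects (35 EG and 35 CG"). It then moves from the number needed to the number enrolled: "considering the potential drop-out rate, 20% more, i.e., a total of 84 patients (42 EG and 42 CG), should be enrolled".

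The Abstract and section 2.3 (Sample Population and Randomization) repeat 84 as the recruitment target. No other drop-out figure appears in the article. The article also gives no effect size, standard deviation, test or sidedness for the calculation behind the 70.

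**The concern.** An allowance for drop-out should leave the required number of patients after the loss has occurred. The loss applies to everyone enrolled, so the enrolled number has to be the required number divided by the retained fraction. Adding the same percentage to the required number gives a smaller total, because the percentage is then taken of 70 and not of the larger number from which patients actually leave.

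The paragraph gives one percentage and ties it to drop-out. A reader will therefore tend to conclude that a 20% loss still leaves 70 evaluable patients and 80% power. It does not. What is at stake is whether the stated target gives the protection a reader would take from it. The validity of the trial is not in question.

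**Working it through.** **Inputs, all from section 3.5**

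- Required: 70 in total, 35 per arm
- Planned power 80%, alpha 5%
- Allowance: 20%
- Enrolment target: 84 in total, 42 per arm (1:1)

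**Step 1. Reproduce the plan's figure.** Adding 20% of the requirement: 70 × (1 + 0.20) = 84, and 35 × 1.20 = 42 per arm. This matches exactly, so this is how the target was formed.

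**Step 2. What remains of 84 if 20% drop out.** 84 × (1 − 0.20) = 67.2, about 67 patients (33.6 per arm). Shortfall against the requirement: 70 − 67 = 3 evaluable patients.

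**Step 3. The largest drop-out that 84 can absorb.** 1 − 70/84 = 14/84 = 16.7%, that is 14 patients.

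**Step 4. The number that would cover 20%.** 70 / (1 − 0.20) = 87.5, rounded up to 88 (44 per arm), which is 88 − 84 = 4 more than planned.

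**Step 5. Evaluable patients from 84 over a range of drop-out.**

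| Drop-out | Evaluable of 84 | Against 70 |
|---|---|---|
| 10% | 75.6 | +5.6 |
| 15% | 71.4 | +1.4 |
| 16.7% | 70.0 | 0 |
| 20% | 67.2 | −2.8 |
| 25% | 63.0 | −7.0 |

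**Step 6. Effect on power.** The article does not give the effect behind the 70, so it has to be assumed. I take the standardised difference d that 35 per arm detects with 80% power at alpha 5%, and recompute power with the reduced numbers.

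- Two-sided two-sample t-test: d = 0.679 at 35 per arm. Power is 78.3% at 33.6 per arm, and 78.2% with whole patients (34 and 33).
- Two-sided normal approximation: d = (1.960 + 0.842) × √(2/35) = 0.670. At 33.6 per arm, power = Φ(0.670 × √(33.6/2) − 1.960) = 78.4%.
- One-sided normal approximation: d = 0.594, power 78.6% at 33.6 per arm.

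All three give a power between 78% and 79%, so the loss at 20% drop-out is between 1 and 2 percentage points whichever version is used.

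**The case against.** The strongest reply is that the sentence does not state a 20% drop-out rate. Grammatically, the words "considering the potential drop-out rate, 20% more" can describe the size of the enrolment increase, and 20% on top of 70 is exactly 84. On that reading the sentence contains no arithmetic error: it sets a 20% margin against a drop-out rate that is left unquantified. This stands as a possible reading, and it is why the point has to be put conditionally. It does not remove the point. The 20% is the only percentage given and sits in the same clause as the drop-out rate, so most readers will take it as the loss that is covered. Under the margin reading, the rate actually covered is 16.7%, and the article does not say so.

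The second reply is that the consequence is slight. That is correct. Up to 16.7% drop-out there is no shortfall at all. At 20% the gap is 3 evaluable patients and less than 2 points of power, and even this power figure rests on a back-calculated effect and an assumed test.

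Two stronger readings are tempting, and the article supports neither.

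- A reader might infer that the trial is underpowered as planned. The shortfall arises only if drop-out exceeds 16.7%, and nothing in the article predicts that it will.
- A reader might infer that patients who interrupt treatment, listed among the exclusion criteria in section 2.2, use up the same 14-patient allowance. Section 2.4 says that both groups are assessed by intention to treat, so a patient who interrupts treatment may still be assessed at T1 and T2. The article does not say that such patients leave the primary analysis or count as drop-outs.

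**Conclusion.** The point holds in conditional form and is minor. The enrolment target is the requirement multiplied by 1.2. It keeps 70 evaluable only up to 16.7% drop-out (14 patients). If the 20% is meant as the drop-out rate, about 67 remain, 3 fewer than the number stated as needed.

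The head counts follow from the article's own figures and need no assumption beyond that reading. The power of about 78% at 20% drop-out additionally assumes a two-sided two-sample t-test and a true effect equal to the one that 35 per arm detects at 80% (d about 0.68). Whether 70 is itself the right base cannot be judged, because the article does not report the effect size and standard deviation used.

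**What to change.** Keep 84 and replace the drop-out sentence in section 3.5 with one that says what the number covers, for example: *Enrolling 84 patients (42 per arm) allows for drop-out of up to 16.7% (14 patients) while keeping 70 evaluable. At 20% drop-out about 67 would remain; assuming a two-sided two-sample t-test and the effect detectable with 80% power at 35 per arm, power would then be about 78%.* The condition on the power figure should stay in the sentence.

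This wording is correct under either reading of the 20%. It costs one sentence and a slightly less favourable stated figure, with no extra patients and no change to the Abstract or section 2.3.

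For reference, full cover of 20% drop-out would correspond to 88 patients (44 per arm). That is 4 more than planned and would require the target to be changed wherever it appears.

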## 4. Discussion

This multicenter, single-blinded RCT represents the first attempt to prove the superiority of a 3D task-specific UL-RAT delivered by a powered exoskeleton over time-matched, conventional arm rehabilitation in a large cohort of subacute stroke patients. The first weeks after a stroke are a critical time window for motor recovery [21], and the role of rehabilitation in this phase is to promote neural repair and the optimization of functioning. It has been shown that early, intensive, repetitive, and task-oriented training may lead to better functional recovery, and such training can be better provided with a robot than with conventional physiotherapy. In fact, robotic rehabilitation can be applied in the very early phases of the disease, and the robot can help perform more intensive, repetitive, and reproducible training. This is why patients who may benefit more from robotics are those more severely affected and within the first months after the event [2].

The expected results of the present multicenter RCT will be (a) to achieve better motor recovery in terms of motor functioning following UL-RAT through the exoskeleton system, thus obtaining greater autonomy in the performance of the ADL and better participation; (b) to identify a customizable rehabilitation protocol for upper limb motor recovery based on the clinical characteristics of the patient (in order to move toward personalized medicine); (c) to classify the clinical and neurophysiological characteristics for the prediction of rehabilitation outcomes in terms of motor recovery; and (d) to investigate if the acquired rehabilitative effects might also be maintained at follow-up.

Concerning the second point, it is conceivable that the better recovery expected in patients receiving the UL-RAT might be related to both the use of the UL exoskeleton and the 2D non-immersive virtual reality during the training [22].

The study design represents a strength of the research. In fact, a stratification of the sample in blocks by time since the event and by severity ensures that the groups are not biased by such determinant variables. In addition, the method used allows us to understand the influence of stroke time and severity on the efficacy of robot-assisted therapy. Future research should focus, as also underlined by the Cochrane revision [2], on the effect of dose and frequency of robotic therapy on the primary outcome, designing pragmatic trials specifically for these objectives (and not verifying them as secondary objectives).

Indeed, it has been shown that visual feedback leads to greater involvement, motivation, and participation of the patients with better functional outcomes. Non-immersive virtual reality has a positive impact not only on motor recovery but also on cognitive function and, therefore, on mood and behavior. Neural plasticity is boosted by virtual reality thanks to the task-oriented exercises, as well as the visual and acoustic feedback that provides the patients with knowledge about both their performance and their results, further favoring reinforcement learning [23,24,25].

In this protocol, the neuroplasticity changes underpinning motor recovery will be assessed in terms of the use of EEG. In fact, as demonstrated for the lower limb, the tool is capable of detecting specific markers (e.g., premotor-parietooccipital desynchronization of γ-oscillations) of the activation of sensorimotor and visuo-spatial associative areas concerning motor planning and selective muscle activation [26]. Moreover, a specific EEG analysis may be used as a predictor of UL post-stroke functional recovery [15,26].

This protocol has some limitations. Firstly, spontaneous recovery will be the main determinant for the trajectories of the obtained recovery. Therefore, it will be difficult to separate the observed time-dependent changes over time, discriminating how much they are due to biological processes or the rehabilitation interventions and environments. To overcome this specific issue, a stratification for time since stroke has been planned. Secondly, the neurophysiological and kinematic assessment will be conducted in a subgroup of patients, preventing us from drawing definite conclusions on the differences among treatments on the brain dynamics and quality of arm movements.

